### Randomisation

The trial will be cluster-randomised to prevent within-school contamination. Schools will be allocated to intervention or control group using minimisation based on geographical location and proportion of children with free school meals (a proxy for deprivation) by a trial statistician at York Trials Unit using dedicated software (MinimPY [25]). Randomisation will occur following baseline data collection. Schools will be informed of their allocation via email. Schools will be advised to tell the parents/carers of participating children the schools random allocation.

Children in schools allocated to the intervention group will receive E-PLAYS plus whatever constitutes care as usual in their school. Participating children in schools allocated to the control group will receive whatever constitutes care as usual in their school. ‘Care as usual’ is defined as the existing support routinely provided for a child with social communication difficulties from educational and health services.

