### Primary outcome analysis (focal children)

The planned primary analysis model will include all available post-randomisation TPS [26] scores as outcomes, modelling these measurements using a linear mixed effect model. This model will include fixed effects for treatment group, time point, and their interaction, and will also condition on fixed effects for baseline TPS mean composite score, year group, child FSM status, geographical location of school, and school level random intercepts. Correlation between repeated measurements within participants will be modelled using an unstructured covariance matrix for the model residuals. Precise details of the terms included in the model will be provided in the SAP (including plans for dealing with any incomplete baseline covariate data). If the fit of the planned primary analysis model is reasonable (see below), then the fitted model will be used to estimate differences (Intervention – Control) in expected TPS scores at both post-randomisation time points, together with 95% confidence intervals and p-values for tests of H_0_: $$\delta$$ = 0 (where $$\delta$$ is the difference in expected score at the relevant time point).

The appropriateness of key model assumptions will be checked using diagnostic plots based on the standardised residuals from the fitted model. If these plots (or indeed other extra-data considerations) suggest the observed data show important departures from the assumptions of the planned analysis, then we will undertake semi-parametric analyses of the scores at each post-randomisation time point in isolation. This will be accomplished using cumulative probability models based on ordinal regression [36]. The ordinal regression models will include fixed effects for treatment group, baseline TPS [26] mean composite score, year group and child FSM status, and a random intercept for school.

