### Sensitivity analyses (Focal children)

Several additional planned analyses of the primary outcome will be undertaken to investigate the sensitivity of the results of the primary analysis to departures from the key statistical assumptions that underpin this analysis. In particular, we will investigate the impact that various alternative adjustment sets have on the results of the primary analysis, investigate the potential impacts of departures from the planned schedule of assessments, and undertake analyses of the primary outcome under different assumptions about any missing primary outcome data.

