### Principal stratum analyses (Focal children)

Participants allocated to the control group will not have access to the E-PLAYS intervention. Participants allocated to the intervention group will be offered the E-PLAYS intervention, but may not receive any sessions at all, or may receive only a proportion of the planned ten sessions (or potentially none of them).

We will estimate two different CACE estimands under different definitions of compliance: (1) The difference in expected TPS mean composite score at 35–40 weeks among participants that would complete at least one session of the E-PLAYS programme if they were randomised to E-PLAYS; (2) The difference in expected TPS mean composite score at 35–40 weeks among participants that would complete at least seven E-PLAYS sessions (70% of the programme) if they were randomised to E-PLAYS.

We will use instrumental variable estimators to estimate both of these principal stratum estimands. Specifically, we will use random allocation as an instrument for the relevant definitions of treatment receipt in each case, with estimation performed using a generalised two-stage least squares random effects estimator. These analyses will include the same baseline covariates as included in the primary analysis and random intercepts for school cluster. Point estimates of the two principal stratum estimands outlined above will be reported together with two-sided 95% confidence intervals and p-values for tests of H_0_: $$\delta$$ = 0.

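### Schools are minimised on school-level free-school-meal proportion, but the primary model as listed adjusts only for the child's own FSM status, so one of the two allocation factors is missing

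*Protocol article*

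**What the plan says.** Under Randomisation, the protocol article gives two allocation factors, both measured on the school: "Schools will be allocated to intervention or control group using minimisation based on geographical location and proportion of children with free school meals".

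Under Primary outcome analysis (focal children), the linear mixed model lets the treatment effect differ by follow-up time. Its remaining terms are given thus: "condition on fixed effects for baseline TPS mean composite score, year group, child FSM status, geographical location of school, and school level random intercepts". Child FSM status is a separate, individual item. According to the Child consent procedure section, it is supplied by the school with parental consent.

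If diagnostics are poor, a semi-parametric fallback is used: "The ordinal regression models will include fixed effects for treatment group, baseline TPS [26] mean composite score, year group and child FSM status", plus a random intercept for school. Location is not in that list.

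Three other statements bear on the point:

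- On the primary model: "Precise details of the terms included in the model will be provided in the SAP".
- Under Sensitivity analyses (Focal children): "we will investigate the impact that various alternative adjustment sets have on the results of the primary analysis". The sets are not named.
- Under Principal stratum analyses (Focal children), for the CACE estimates: "These analyses will include the same baseline covariates as included in the primary analysis".

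Continuous secondary outcomes are to be analysed in a similar way to the primary outcome, and the Partner analysis also follows a similar approach. Neither section says that the covariates are identical.

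**The concern.** Minimisation forces the arms to be alike on school FSM proportion. Any outcome variation tied to that factor then no longer adds to the true sampling variance of the treatment contrast. A model without the factor does not know this. It leaves the variation in the school random intercept and counts it as noise. The reported standard error is then too large for the allocation actually used, the confidence interval is too wide, and the test rejects a true null less often than 5% of the time.

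Child FSM status closes only part of the gap. With a mean of 4.55 Focal children per school, their own statuses are a noisy stand-in for the school's proportion, and a school's deprivation level may relate to outcome beyond one child's status. The article gives no reason for changing level on FSM while keeping location at school level.

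What is at stake is precision, in a trial whose planned power has already come down from 90% to about 85.2%.

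**Working it through.** **Inputs from the article (Sample size calculations, Revised).** Difference 2 points; SD 7; pre-post correlation 0.6; ICC 0.05; mean cluster size 4.55; attrition 20%; 44 schools per arm. The two-sided 5% alpha is from the Original subsection.

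**Input not in the article (assumption).** R² is the share of between-school variance explained by school FSM proportion, net of baseline TPS, child FSM status and location. The main range used is 20% to 50%; 0 and 100% are shown as limits. Balance on the factor is taken as perfect.

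**Step 1: reproduce the plan's power.**
- Adjusted SD = 7 × √(1 − 0.6²) = 5.6, so the variance is 31.36.
- Analysed per school: 4.55 × 0.8 = 3.64.
- Between-school variance: 0.05 × 31.36 = 1.568. Within-school variance: 0.95 × 31.36 = 29.792.
- SE₀ = √[2 × (1.568/44 + 29.792/(44 × 3.64))] = √[2 × (0.03564 + 0.18601)] = 0.6658.
- Power = Φ(2/0.6658 − 1.960) = Φ(1.044) = 85.2%, which matches the stated figure.

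**Step 2: three quantities for each R².**
- True SE when the factor is balanced: SE₁ = √[2 × (1.568 × (1 − R²)/44 + 0.18601)].
- Factor included: power = Φ(2/SE₁ − 1.960).
- Factor balanced but omitted: the estimate varies with SE₁, but the test uses SE₀. Power = Φ((2 − 1.960 × SE₀)/SE₁), and type I error = 2 × [1 − Φ(1.960 × SE₀/SE₁)].

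| R² (ICC 0.05) | SE₁ | Power, omitted | Power, included | Gain (points) | Type I error, omitted |
|---|---|---|---|---|---|
| 0 | 0.666 | 85.2% | 85.2% | 0 | 0.050 |
| 20% | 0.655 | 85.6% | 86.3% | 0.7 | 0.046 |
| 50% | 0.638 | 86.2% | 87.9% | 1.8 | 0.041 |
| 100% | 0.610 | 87.3% | 90.6% | 3.4 | 0.032 |

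At R² of 20% and 50% the reported SE is too large by 0.6658/0.6550 = 1.6% and 0.6658/0.6385 = 4.3%.

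**Step 3: a smaller ICC.** The Original subsection reports a feasibility ICC below 0.01. With ICC 0.01, SE₀ = 0.634. At R² = 20% power is 88.5% omitted and 88.6% included, a gain of 0.1 points. At 50% it is 88.6% and 88.9%, a gain of 0.3 points. Type I error when omitted is 0.049 and 0.048.

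**Step 4: rough check by simulation.** There were 1,500 runs per setting, with minimisation of 88 schools on an assumed two-level FSM factor and an assumed four-level location factor, and child FSM kept in both models. At ICC 0.05, power without and with the school factor was 82.0% and 82.9% (R² 25%), 83.3% and 85.6% (50%), and 83.5% and 86.8% (100%). At ICC 0.01 the gap never exceeded 0.7 points. The Monte Carlo standard error of a 5% rejection rate is √(0.05 × 0.95/1500) = 0.006, so the simulation supports the direction and rough size of the power gap, but does not measure the type I error closely.

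**The case against.** The strongest case on the other side has four parts.

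- **Validity is not harmed.** This stands. The omission causes no bias, and type I error stays at or below 5%. A reader might infer that leaving out an allocation factor makes the primary result invalid. Nothing in the article supports that; the cost is lost precision.
- **The benefit is small and rests on an assumption.** This also stands. The article does not say how much variance school FSM explains, and the relevant share is only what baseline TPS, child FSM status and location leave unexplained. Baseline TPS correlated 0.79 with the 35–40-week score in the feasibility trial. The ICC of 0.05 is a deliberate allowance for all levels of clustering; near the observed value the gain almost vanishes. A reader might also compare the plan's 85.2% with 86.3% to 87.9% and infer a gain of 1.1 to 2.7 points. That overstates it, because 85.2% gives no credit for balance that minimisation has already achieved.
- **The article defers to the SAP and plans alternative adjustment sets.** This stands in part. The SAP is not at hand and could add the term, so it cannot be said that the final analysis will lack it. But the article does print a specific list, with one allocation factor at school level and FSM at child level. Unnamed sensitivity analyses do not correct the primary interval or p-value.
- **The reach is limited.** This stands. A reader might infer that the same covariates bind every later analysis. Only the CACE section says so; the secondary and Partner sections describe a similar approach.

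**Conclusion.** The mismatch is plain on the text: of the two factors used to allocate schools, the listed primary model contains one, and the fallback ordinal model contains neither. The result is a slightly conservative test and intervals that are slightly too wide, with no bias.

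On the plan's own inputs, the loss is about 0.7 to 1.8 percentage points of power if school FSM explains 20% to 50% of the residual between-school variance. It is about 3.4 points at the limit where school FSM explains all of it, and about 0.3 points or less at ICC 0.01 over the 20% to 50% range. These figures assume perfect balance on the factor and a normal approximation. The type I error and power calculations were made for the primary mixed model only, not for the ordinal fallback.

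This is a modest point, worth correcting before analysis because the correction is nearly free.

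**What to change.** - **Primary model:** add school-level FSM proportion as a fixed effect, in the form used for minimisation, beside location. Child FSM status can stay as an additional prognostic covariate.
- **CACE analyses:** these then gain the term automatically, since they use the primary covariates.
- **Fallback ordinal model:** add both school FSM proportion and location.
- **Secondary and Partner analyses:** state that the term is carried into these too.

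The cost is one added covariate in the primary model and two in the fallback, written into the SAP and reported as a change from the article's list. No new data are needed: the school's FSM proportion had to be known to allocate it.

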### Sensitivity analyses (Focal children)

Several additional planned analyses of the primary outcome will be undertaken to investigate the sensitivity of the results of the primary analysis to departures from the key statistical assumptions that underpin this analysis. In particular, we will investigate the impact that various alternative adjustment sets have on the results of the primary analysis, investigate the potential impacts of departures from the planned schedule of assessments, and undertake analyses of the primary outcome under different assumptions about any missing primary outcome data.

### Principal stratum analyses (Focal children)

Participants allocated to the control group will not have access to the E-PLAYS intervention. Participants allocated to the intervention group will be offered the E-PLAYS intervention, but may not receive any sessions at all, or may receive only a proportion of the planned ten sessions (or potentially none of them).

We will estimate two different CACE estimands under different definitions of compliance: (1) The difference in expected TPS mean composite score at 35–40 weeks among participants that would complete at least one session of the E-PLAYS programme if they were randomised to E-PLAYS; (2) The difference in expected TPS mean composite score at 35–40 weeks among participants that would complete at least seven E-PLAYS sessions (70% of the programme) if they were randomised to E-PLAYS.

We will use instrumental variable estimators to estimate both of these principal stratum estimands. Specifically, we will use random allocation as an instrument for the relevant definitions of treatment receipt in each case, with estimation performed using a generalised two-stage least squares random effects estimator. These analyses will include the same baseline covariates as included in the primary analysis and random intercepts for school cluster. Point estimates of the two principal stratum estimands outlined above will be reported together with two-sided 95% confidence intervals and p-values for tests of H_0_: $$\delta$$ = 0.

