### Intervention

The E-PLAYS programme is designed for children with SCDs aged 5–7 years old (referred to hereafter as ‘Focal’ children). Using a computer game, E-PLAYS guides the Focal child through real-life conversational exchanges with a specific focus on (a) requesting optimally useful information (b) giving helpful directions and (c) asking for clarification. Each Focal child is matched with a ‘Partner’; a typically-developing child from the same year group.

Each E-PLAYS session uses the computer game which is designed for two players using interlinked laptops. There are ten weekly sessions of 30 min each; schools’ teaching assistants are trained to deliver and supervise all sessions. Five sessions are with the Focal child and the teaching assistant only, five are with the Focal and Partner child together supervised by the teaching assistant. Sessions with the classmate (Partner child) give the child an opportunity to practice newly-acquired skills and also to learn collaboration skills through joint problem-solving with a peer. E-PLAYS is web-based, enabling us to distribute E-PLAYS directly to schools. Teaching assistants will self-train using a comprehensive manual with online support. The E-PLAYS software automatically records the number of sessions along with date accessed and sends this data directly to the research team.

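### The CACE for at least seven sessions gives the stated stratum effect only if one to six sessions do nothing; if partial delivery helps, it is too large

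*Protocol article*

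**What the plan says.** In the protocol article, the section on principal stratum analyses of Focal children describes non-compliance on one side only. On the control side, "Participants allocated to the control group will not have access to the E-PLAYS intervention". On the intervention side, children may receive nothing, "or may receive only a proportion of the planned ten sessions".

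Two CACE estimands follow, both for TPS at 35–40 weeks. The first is the effect "among participants that would complete at least one session of the E-PLAYS programme if they were randomised to E-PLAYS". The second is the effect "among participants that would complete at least seven E-PLAYS sessions (70% of the programme) if they were randomised to E-PLAYS".

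One identification strategy serves both: "we will use random allocation as an instrument for the relevant definitions of treatment receipt in each case". The estimator is likewise common to both, a random effects form of generalised two-stage least squares. The models use the primary analysis covariates and random school intercepts. Each estimate is to be reported with a 95% confidence interval and a p-value.

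The section on sensitivity analyses covers the primary analysis only: adjustment sets, assessment timing and missing outcome data. The section on fidelity analysis says that the software records each child's number of sessions and that these data feed the CACE analyses.

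**The concern.** When receipt means seven or more sessions, a child with one to six sessions is coded as untreated. That child's outcome still enters the intervention arm mean, so any gain from partial delivery is in the numerator (the effect of allocation) while the child is missing from the denominator (the share treated). The gain is credited to the children who reached seven sessions. The calculation recovers the named stratum effect only under an exclusion restriction: allocation must have no effect on TPS in children who would receive fewer than seven sessions.

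The article offers no support for that assumption. The Intervention section states "There are ten weekly sessions of 30 min each", so six sessions are 6 × 30 = 180 minutes out of 300.

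At stake are the size and interval of an estimate that schools may read as the effect of fuller delivery. There is also a presentational risk. The two CACEs rescale essentially the same allocation effect, so the seven-session figure will be further from zero whenever some children stop at one to six sessions. Side by side, the pair can look like a dose-response.

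**Working it through.** **The plan's own figures.** The article states no figure for the CACE analyses. Its effect size, 2 TPS points, sets the scale below. The revised design figure reproduces:
- analysed per arm: 44 × 4.55 × 0.8 = 160.16
- design effect: 1 + (0.8 × 4.55 − 1) × 0.05 = 1.132
- residual SD: 7 × √(1 − 0.6²) = 5.6
- power: 85.17%, against about 85.2% stated

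**Inputs.**
- From the article: no control access, the two definitions of receipt, allocation as instrument, two-stage least squares.
- Assumed, because the article does not give them: the share with one to six sessions (p₁₋₆, 10–30%), the share with seven or more (p₇, 60–85%), and the effect of one to six sessions (d₁₋₆) as a fraction of the effect of seven or more (d₇). The true d₇ is set to 2 points.

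**Formulas.** Children with no sessions contribute no effect, so:
- ITT = p₇·d₇ + p₁₋₆·d₁₋₆
- target of the seven-session analysis = ITT / p₇ = d₇ + (p₁₋₆/p₇)·d₁₋₆
- target of the one-session analysis = ITT / (p₇ + p₁₋₆), the average effect among all children with any exposure

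The one-session target matches its estimand for any d₁₋₆. The seven-session target matches d₇ only if d₁₋₆ = 0 or no child stops at one to six sessions.

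**One case in full.** With p₁₋₆ = 0.20, p₇ = 0.70 and d₁₋₆ = 1, ITT = 0.70 × 2 + 0.20 × 1 = 1.6. The seven-session target is 1.6/0.70 = 2.29 against a truth of 2 (+14%).

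**Range** (seven-session target when the truth is 2):

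| Share 1–6 / 7+ | Partial effect 25% of full | 50% | 100% |
|---|---|---|---|
| 10% / 85% | 2.06 (+3%) | 2.12 (+6%) | 2.24 (+12%) |
| 20% / 70% | 2.14 (+7%) | 2.29 (+14%) | 2.57 (+29%) |
| 30% / 60% | 2.25 (+13%) | 2.50 (+25%) | 3.00 (+50%) |

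With a partial effect of zero the bias is zero. With a harmful partial effect the bias is downward: for example 1.86 (−7%) at 20%/70% if the partial effect is −25% of the full effect.

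**Simulation.** Ordinary two-stage least squares was run with a baseline covariate in 88 clusters, with 10%, 20% and 70% of children at 0, 1–6 and 7+ sessions. Mean estimates were 1.95, 2.27 and 2.60 for partial effects of 0%, 50% and 100%. The formula gives 2.00, 2.29 and 2.57. The Monte Carlo standard error is 0.02, and all three means lie within about 0.05 of the formula.

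**The two CACEs side by side.** Their ratio is (ITT/p₇) / (ITT/(p₇ + p₁₋₆)) = P(≥1)/P(≥7). With 90% and 70% this is 0.90/0.70 = 1.29, whatever the dose-response:
- Partial effect equal to full: ITT = 1.8, and the estimates are 1.8/0.90 = 2.00 and 1.8/0.70 = 2.57, although both true effects are 2.
- Partial effect zero: ITT = 1.4, and the estimates are 1.4/0.90 = 1.56 and 1.4/0.70 = 2.00, both correct.

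The pair cannot tell these situations apart.

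**The case against.** The strongest reply is that nothing in the article shows partial delivery to have an effect. A reader might infer that the exclusion restriction is violated and the estimate therefore inflated. The article does not support that: the restriction fails only if one to six sessions change TPS at 35–40 weeks, and no such effect is reported. This stands. What remains is that the estimate depends on a zero effect for which the article gives no justification.

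A reader might also infer that the two estimands contradict each other, since a child with three sessions counts as treated in one and untreated in the other. They do not. The first averages over everyone with at least one session and assumes nothing about the size of the effect at one to six. Only the second needs that effect to be zero. Both definitions are declared openly.

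A third reply is that identifying assumptions and sensitivity analyses for a supplementary estimand belong in the SAP, which is not shown. Their absence from the article is indeed no fault. But the article itself fixes the estimand, the binary receipt variable, the instrument and the estimator, and that combination is what can miss its target.

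Finally, a model on the number of sessions is not clean either. Take effects of 2 points at 7+ and 1 point at 1–6, and assume mean sessions of 8.5 and 3.5 in the two bands. With shares of 70%/20%, mean sessions are 0.7 × 8.5 + 0.2 × 3.5 = 6.65. Scaled to ten sessions the model gives 1.6/6.65 × 10 = 2.41, further from 2 than the 2.29 above. Most of that gap comes from comparing a ten-session effect with one at an average of 8.5. Scaled to 8.5 it gives 2.05, and 1.5/6.15 × 8.5 = 2.07 at 60%/30% and 1.4/5.65 × 8.5 = 2.11 at 50%/40%. The model is useful beside the seven-session analysis, but it assumes linearity and answers a different question.

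**Conclusion.** The point holds in conditional form. The seven-session CACE identifies its stated principal stratum effect only if one to six sessions have no effect on TPS at 35–40 weeks. If partial delivery is beneficial, the estimate is too large by (p₁₋₆/p₇) × that effect, about 3% to 50% over the assumed ranges. The size cannot be fixed from the article, and with few partial completers it is small.

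A reader might take this as a threat to the trial's main conclusion. It is not. The primary analysis compares groups as randomised, and the one-session CACE is sound on this point. The p-value for the seven-session analysis is in effect a test of no allocation effect, so no new route to a false positive arises. What is affected is the size and interval of one supplementary estimate, and the reading of the two CACEs as a pair.

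**What to change.** Before analysis, in the SAP:

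1. Keep the one-session CACE as the main instrumental-variable estimand.
2. Report the seven-session estimate with its no-effect assumption stated and a sensitivity analysis over the effect of one to six sessions. Writing d₁₋₆ = f·d₇ gives d₇ = ITT / (p₇ + f·p₁₋₆), with f running from 0 to 1. At f = 0 this is the planned estimate; at f = 1 it equals the one-session CACE. In the worked case with f = 0.5 it returns 1.6 / (0.70 + 0.5 × 0.20) = 2.00. For a beneficial effect, label the planned estimate an upper bound if partial delivery is assumed not harmful.
3. Add an instrumental-variable model with the logged number of sessions as the treatment variable, alongside the seven-session analysis and not in its place.
4. Say in the report that the gap between the two CACEs reflects the two compliance shares and is not evidence of dose-response.

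The cost is some SAP wording and a little more analysis; no new data are needed. The session-count model assumes a linear effect per session and targets a different estimand, and the report should say so.

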#### Revised

For the 20 school clusters recruited as part of the internal pilot phase, the observed mean cluster size (at randomisation) was 4.55 participants per cluster, around 25% less than the anticipated six participants per cluster detailed in the previous section.

Following discussion with the funder, the total target number of school clusters was changed to 88. Assuming a mean cluster size (at randomisation) of 4.55 and keeping all assumptions the same as previously (e.g.$$\delta$$ = 2, SD = 7, pre-post correlation = 0.6, school level intra-cluster correlation of 0.05 and 20% participant level attrition), 44 clusters per group would provide approximately 85.2% power for a two sided test of $${H}_{0}:\delta =0$$ (where $$\delta$$ is the difference in expected TPS score at 35–40 weeks).

As per the original proposal we will randomly select one Partner child per school to complete the primary outcome (TPS [26],) at baseline and 15–20- and 35–40-weeks post-randomisation. Under the same assumptions as before, a sample size of 88 children (one per school) will give 80% power to detect a difference of 3.4 points in the TPS [26].

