### Statistical analysis plan

Statistical analysis will primarily be conducted in Stata/MP v18 [35] or later, unless specified otherwise. All analyses will be conducted just once at the end of the trial follow-up period, according to precise specifications detailed in a Statistical Analysis Plan (SAP) that will be approved by the TMG and TSC prior to the end of follow-up. Any departures from the analysis plan will be reported and justified in the final trial reports and other relevant published articles.

The flow of clusters and participants through the study will be presented according to CONSORT guidance for cluster RCTs. Continuous characteristics will be summarised in terms of the available sample size, arithmetic mean, standard deviation, median, interquartile range, minimum and maximum. Categorical characteristics will be summarised in terms of frequencies and percentages.

For all between group comparisons, clusters and participants (both Focal and Partner) will be analysed as part of the groups to which they were randomised, regardless of subsequent engagement with the allocated treatment. All analyses estimating between group contrasts will include all participants with data available for the relevant outcome (unless explicitly stated otherwise in the SAP). Point estimates of contrasts between randomised groups will be reported together with appropriate 95% confidence intervals. Point and interval estimates will be reported on the scale of the original measurements (as well as the scale used for the analysis should these differ). P-values for statistical tests will be two-sided unless specified otherwise in the SAP.

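### The CACE analyses use only children with a 35–40-week TPS, so they rest on a stronger missing-data assumption than the primary estimate at the same time point

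*Protocol article*

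**What the plan says.** All references are to the protocol article.

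- **Principal stratum analyses.** The first estimand is "The difference in expected TPS mean composite score at 35–40 weeks among participants that would complete at least one session" of E-PLAYS if offered it. The second has the same outcome and time point but requires at least seven sessions. Allocation is the instrument, "with estimation performed using a generalised two-stage least squares random effects estimator". On adjustment: "These analyses will include the same baseline covariates as included in the primary analysis and random intercepts for school cluster". The 15–20-week TPS does not appear, and no imputation is named.
- **Primary outcome analysis (focal children).** "The planned primary analysis model will include all available post-randomisation TPS [26] scores as outcomes", and "Correlation between repeated measurements within participants will be modelled using an unstructured covariance matrix for the model residuals". If the fit is poor, ordinal models are fitted to each follow-up visit separately.
- **Statistical analysis plan (default population).** "All analyses estimating between group contrasts will include all participants with data available for the relevant outcome (unless explicitly stated otherwise in the SAP").
- **Sensitivity analyses (Focal children).** The team will "undertake analyses of the primary outcome under different assumptions about any missing primary outcome data". The section is framed around the primary analysis, and the CACE is not mentioned.
- **Sample size, Revised.** The planning assumption is "20% participant level attrition".

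**The concern.** Two effects are to be reported for the same outcome at the same visit: the ITT difference and the difference among compliers. A reader will expect the second to be close to the first divided by the proportion who received E-PLAYS. As written, they come from different sets of children and rest on different assumptions.

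The mixed model is valid if missingness at 35–40 weeks is unrelated to the unseen score given arm, baseline covariates and the 15–20-week TPS. The two-stage estimator is valid only if that holds given arm and baseline covariates alone. If loss after the first follow-up is related to how the child scored there, the ITT estimate is protected and the CACE is not. The two could then diverge because of missing-data handling alone, and the divergence could be read as information about compliers.

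**Working it through.** **1. The plan's own figure.** Inputs from the revised sample size section: difference 2, SD 7, pre-post correlation 0.6, ICC 0.05, 44 schools per arm, 4.55 children per school, 20% attrition.

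- Residual SD = 7 × √(1 − 0.6²) = 5.6
- Children followed per school = 4.55 × 0.8 = 3.64
- Design effect = 1 + (3.64 − 1) × 0.05 = 1.132
- Effective n per arm = 44 × 3.64 / 1.132 = 141.5
- SE of the ITT difference = 5.6 × √(2/141.5) = 0.666
- Power = Φ(2/0.666 − 1.96) = 85.2%, as stated

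**2. How many children are at issue.** 88 × 4.55 = 400 Focal children, of whom 20%, about 80, would lack a 35–40-week TPS. The CACE loses all of them. The mixed model recovers those with a 15–20-week score. The protocol does not say how many that would be, so it is varied below.

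**3. Scale for the CACE.** Assume 85% receipt (not in the protocol). True CACE = 2/0.85 = 2.35 points. SE ≈ 0.666/0.85 = 0.78 points.

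**4. Simulation at assumed correlations.** Large-sample; baseline with 15–20 weeks 0.65, baseline with 35–40 weeks 0.60, between follow-ups 0.75. 20% of 35–40-week scores are missing. The odds of being missing rise as the 15–20-week TPS falls, by the odds ratio (OR) per SD, with the score centred within arm.

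| Dropout depends on the 15–20-week TPS in | Bias of available-case CACE | In points (× 2.35) |
|---|---|---|
| Both arms alike | about 0 to −1% | about 0 to −0.02 |
| Intervention arm only, OR 1.5–2 | +10% to +16% | +0.24 to +0.38 |
| Intervention arm only, OR 2, half of losses have a 15–20-week score | about +8% to +9% | +0.19 to +0.21 |
| Intervention arm only, OR 1.5–2, a quarter of losses have one | +3% to +6% | +0.07 to +0.14 |
| Intervention arm only, OR 4 | +28% | +0.66 |

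The ITT estimate that uses the 15–20-week score, divided by receipt, stayed within about 1% of 2.35.

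**5. Range over other assumptions.** Receipt 70% or 90% (true CACE 2/0.7 = 2.86 or 2/0.9 = 2.22); OR 2 or 4; every child with a 15–20-week score; score centred on the overall mean. Correlation between follow-ups 0.6 to 0.8 with baseline correlations of 0.6, or 0.84 with the feasibility values 0.84 and 0.79.

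- The joint ITT estimate was 2.00 to 2.03 throughout (truth 2.00).
- CACE bias under the same rule in both arms: −1% to −8%.
- Control arm only: −8% to −40%. Intervention arm only: +8% to +36%. At OR 2 alone, one-arm bias was 8% (feasibility correlations) to about 21% (follow-up correlation 0.8) in absolute size.
- Opposite directions in the two arms, the most extreme case: −16% to −70%.
- No true effect, control-arm-only dependence, OR 2, 70% receipt: ITT 0.00, CACE −0.45. With the same rule in both arms, both were 0.00.
- Missing completely at random: both unbiased (2.00 and 2.86).
- The same instrumental-variable estimator, run before any score was removed, returned 2.22 and 2.86. The bias therefore comes from the missing scores, not from the instrument.

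The simulated estimator omitted the school weighting of the planned random-effects version. At an ICC of 0.05 this should change point estimates little.

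**The case against.** **This is detail for the SAP.** The section never says that children with a missing score are discarded, the default population yields to the SAP, and imputing before the two-stage step is compatible with the text. What stands: the SAP may already deal with this, and the point concerns only what the article fixes. But the article does name the estimator, instrument, covariates and random effects, together with an available-data default. Taken together they have the consequence described.

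**The documents do not contradict themselves.** That is right. Nowhere do they claim that the CACE is the ITT effect rescaled, or that both use the same children.

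**A reader might infer that the CACE will be wrong by a third or more.** One constructed case does give that: random loss in controls and loss falling on low scorers in the intervention arm moves the average estimate from 2.35 to 3.13 (+33%). The documents do not support it. They give one overall attrition figure, with no split by arm or score. Delivery is ten weekly sessions, so planned delivery is over by the 15–20-week assessment, which weakens the idea that failing delivery drives later loss. The section on teaching assistant withdrawal does allow arm-specific loss, since families affected by an unreplaced assistant are asked whether they will go on providing outcomes. It does not tie that loss to the child's score.

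**The contrast is conditional.** This stands. Children missing both follow-ups gain nothing from the mixed model. If the ordinal fallback is used, the ITT analysis loses the same children.

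**The bias is small beside sampling error.** Largely true: 8–16% of 2.35 is 0.19 to 0.38 points, against an SE of about 0.78.

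**Conclusion.** The point holds in a limited form. As written, the CACE needs a stronger missing-data assumption than the primary estimate at the same visit, because it ignores the 15–20-week TPS that the primary model uses.

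The bias is negligible to small (at most 8% in the cases run) if dropout depends on that score alike in both arms. It is roughly 8–16% under moderate one-arm dependence at the assumed correlations, and reaches about 20% if the two follow-ups correlate at 0.8. Larger values need stronger or opposing dependence. The direction depends on which arm loses low scorers: upward for the intervention arm, downward for control.

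These sizes rest on assumed receipt, follow-up correlation and dropout mechanism, none of which the protocol gives. The analysis is supplementary and the primary result is untouched. The documents do not show that the CACE will be biased. They show that it is less protected than it could be at little cost.

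**What to change.** Amend the principal stratum section, or state in the SAP, one of the following as the main CACE estimator:

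1. Multiply impute the 35–40-week TPS separately by arm, using the 15–20-week TPS, sessions completed, baseline covariates and school, then run the planned two-stage estimator on the imputed data. This route does not depend on the mixed model being retained.
2. Where the mixed model is retained, divide its 35–40-week difference by the between-arm difference in the proportion meeting the compliance definition, with a 95% confidence interval from a bootstrap that resamples schools.

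In either case, take receipt from the software's session log for every randomised Focal child for whom it is available. Say how gaps are handled, because data collection stops when a school withdraws and its log may be incomplete. Keep the available-case two-stage estimate as a sensitivity analysis.

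The cost is a few lines of text and a short imputation or bootstrap program. No new data are needed; the downside is a little more analysis work.
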